## **Questionnaire**

At baseline, socio- demographic and medical characteristics of the participants will be collected using an interviewer-administered baseline questionnaire. At each subsequent fortnightly/monthly visit, caretakers will answer a questionnaire about morbidity. Some questions will also assess the adherence to the food supplement (quantities consumed). In addition, all data on morbidity as collected during the clinical examination by a nurse (symptoms, diagnosis and treatments prescribed) will be recorded in a case-report form. All serious AE will be immediately reported to the study supervisor. Childcare behaviors related to supplementary feeding and adherence to and acceptability of the products will furthermore be explored (as described in the section 3.3). The provisional list of information that will be collected is presented in annex 7. In addition dietary data will also be collected at inclusion, 3 and 6 months.

## **Blood sampling and analyses**

Blood samples will be taken at baseline and thereafter at 3 and 6 months of follow-up. An anesthetic crème will be applied to the skin prior to blood sampling to minimize pain.

2.5 ml of venous blood sample will be collected by standard phlebotomy. Directly after taking the blood sample 1 drop of whole blood will be put on filter paper with BHT – to be dried and stored in 4°C. Furthermore, 1 drop will be used to estimate hemoglobin concentration (HemoCue) on the spot and 1 drop will be used for malaria rapid-test on the spot (local standard).

The rest of the blood will be put into a tube and taken to the lab in Yako. At the lab the blood will be centrifuged and the serum added to small tubes, stored at -20°C and then transported to the labs for analysis.

Since no laboratory in Burkina Faso performs all the desired analyses for research purposes, the samples will be exported for analysis.

- 0,2 ml of serum will be send to University of Copenhagen for analysis of IGF-1.
- 0,2 ml of serum will be sent to Germany for analysis of CRP, AGP, ferritin, Retinol Binding Protein, (RBP) soluble Tranferrin Receptor (STR).

---

 Department of Human Nutrition, [name]

- 1 drop of dry blood on filter paper will be sent to Canada for analysis of essential fatty acid status.

As a precaution, remaining serum will be collected in a tube and will be sent and stored at the University of Copenhagen at -80 degrees C for 5 years in anonymous form. Remaining plasma will be used only to measure other indicators of nutritional status (e.g. Hepcidin), growth and infection related to this study. After 5 years the samples will be destroyed. No analyzes other than the ones mentioned here will be performed.

### **Thymic Size**

The size of the thymus will be measured by ultrasound in a subgroup of children at baseline, at 3 months and 6 months.. The Ultrasound device used will be MicroMaxx model from Sonosite, which is portable, durable and resistant to water and dust. It has a long-lived battery and can thus work in a setting with irregular power supply. The measurement is done with the child lying on the back on a pillow or on mothers lap. The transducer with water-based gel on is placed on the chest of the child just over the sternum, and two pictures in two different angles are obtained. Depending on the mood of the child, the whole examination may take 5- 15 minutes.

To assess the effect of moderate malnutrition on thymic size, a reference group of approximately 30 apparently healthy well-nourished children will be invited to participate..The reference group will be recruited among healthy children attending the health centres for vaccinations or as companions to sick siblings. They will be age-matched to the study participants, and for this reason, they will be recruited by the end of recruitment for the main study, so that the age distribution of the participants is known. Otherwise, the inclusion criteria for these children are

- W/H > -1 z-score
- age 6 – 23 months
- no apparent acute or chronic disease

The data that will be collected from these children is the following

- anthropometry
- morbidity questionnaire
- thymus size measured by ultrasound

---

 [name]. [name]

 [name]., Associate Professor, Department of Kinesiology, University of Waterloo, [name]

A separate informed consent form will be made for the healthy controls describing the purpose of the study, the assessments that will be carried out and the risks and benefits associated with these. It will be clearly stated that participation is voluntary and that refusal to participate will not affect the treatment that the child is otherwise receiving.

The consent forms will be translated into the local language and read out to child's caretaker. Each participant will receive a copy of the information sheet and consent form. After giving appropriate time to consider, the caretaker will be asked if his/her child may participate in the reference group, and in case they agree, they will be asked to sign the informed consent form. If the caretaker is illiterate, a thumbprint will be accepted instead of a signature, and in this case, a literate witness is required to sign to confirm that the information material has been read out accurately to the caretaker.

No payment will be given to the caretaker for letting his/her child participate in the study's reference group, however, an incentive (a mosquito-net, or something of similar value) will be given. If any condition requiring treatment is identified during the assessments, the child will be referred for further investigation and treatment.

.

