##### 3.1.2. Study population

Children will be eligible for inclusion if they fulfill the following criteria:

- weight-for-height z-score (WHZ)  $\geq -3$  and  $< -2$  (based on the WHO growth standard) or
- MUAC  $\geq 115$ mm and  $< 125$  mm
- 6 to 23 months of age,
- resident in the catchment area at the time of inclusion,
- whose parents/guardians have signed (or thumb-printed whenever illiterate) the informed consent.

---

 From 7.30am to 4 pm, all year long.

 UNAIDS 2009

 According to the workload, prior MUAC screening might be implemented.

 A local calendar of events will be piloted. If it does not appear suitable for inclusion based on age, children would be included based on a combination of event calendar and height.

Will be excluded:

- Children with severe acute malnutrition defined as a WHZ < -3, and/or a MUAC <115 mm, and/or bilateral pitting oedema. They will be referred to the health centres or Yako hospital for appropriate treatment,
- Children with medical complications requiring hospitalization,
- Children whose household plans to leave the catchment area in the next 6 months.
- Children with a hemoglobin concentration <4g/dl or with evidence of a decompensate anemia (eg, dyspnea, tachycardia...). These children will be transferred to the ITFC supported by ALIMA for appropriate treatment.
- Children who have been treated for SAM or who have been hospitalized in the last 2 months,
- Children with known allergy to milk, peanut, CSB and/or RUTF,
- Children with a severe disability limiting the possibility of investigations,
- Children enrolled in any other nutritional program or part of any other study conducted in the area.

Children with MAM who do not wish to participate in the study or who are excluded due to some of the above mentioned criteria, will be referred to the national supplementary nutritional program currently supported by WFP.

Appropriate free care, including referral to nutritional rehabilitation or pediatric care at Yako hospital (supported by ALIMA) when needed, will be offered to children who are non-eligible due to SAM or decompensated anemia.

Children will be recruited among children presenting spontaneously at the CSPA. All children taken to CSPA will be screened for eligibility. Furthermore active case finding within the community by community health workers supervised by ALIMA will be done.

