### 3.1.13. *Data analysis*

The main effectiveness criterion will be the mean change in lean body mass after 3 months of supplementation (absolute increase expressed in kg). The primary analysis will be conducted in the intention to treat (ITT) population and will therefore include all randomized subjects having at least one exploitable baseline and 3 months LBM measures,. The primary analysis will be conducted by means of a single statistical analysis including both main arms, ie LNS and iCSB:

- A three-way analysis of variance (ANOVA) will be used to evaluate if the two interventions modify the effect of dehulled soy and soy isolate at different levels of milk content.
- The ANOVA will also include LBM at baseline as well as a number of additional explanatory (age, sex, MUAC, WHZ, season) that adjust for potential differences present in the study population. To adjust for variation between centers random effects for each centre are also included in the model. Thus, the statistical model will be based on a linear mixed model.
- Pairwise comparisons of means within and across the two arms will be done using the linear mixed model. Multiplicity will be taken into account by adjusting all pairwise comparisons.
- The effect of supplementation, ie. the difference in mean changes in LBM at 3 months of each group will be presented in terms of estimated means with 95% confidence intervals.

All other statistical analyses of the primary endpoint, ie other study populations, sub-group analysis, and inside-the-table comparisons, and all statistical analyses of secondary endpoints, will be considered secondary analyses. These include:

- Evaluation of the effect of the type of soy by comparing, in the LNS and the iCSBs groups separately, the mean increase in LBM at 3 months over the two groups of soy quality (dehulled soy i.e. 3 groups merged, soy isolate i.e. 3 groups merged).
- Evaluation of the effect of the milk protein content by comparing, in the LNS and the iCSBs groups separately, the mean increase in LBM at 3 months over the three groups of milk protein content (i.e. 2 groups merged for each level of milk).
- Analysis might also be conducted among the subgroup of participants presenting these 2 LBM measurements and the per-protocol population (i.e. excluding participants with violation of protocol).

For all secondary analyses, no adjustment for multiplicity is planned.

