## 5. Study schedule and training

. Training of the field team will be ensured by ALIMA and the PhD students of the University of Copenhagen involved in the project. In addition, all partners will ensure regular support. During the study, continuous supervision, regular meetings and reporting will ensure updating of knowledge and permanent training throughout the study.

Recruitment of the children is expected to begin in August 2013 and last for 6 months (Table 3). For each child, the intervention is scheduled for three months, with an additional three months of follow-up of all children participating in the trial. In total, the study is expected to last for one year including follow-up period.

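### The thymus reference group has no MUAC criterion and is tied to the end of recruitment, so the comparison with MAM children is open to dilution and to seasonal confounding of unknown size

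*Combined protocol and SAP*

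**What the plan says.** Section 3.1.11 (Thymic Size) has the thymus scanned in a subgroup of trial children, of unstated size, at 0, 3 and 6 months. To judge how moderate malnutrition affects the thymus, "a reference group of approximately 30 apparently healthy well-nourished children will be invited to participate". They are to be "recruited among healthy children attending the health centres for vaccinations or as companions to sick siblings". The listed criteria are a weight-for-height z-score above -1, age 6 to 23 months, and "no apparent acute or chronic disease". MUAC is not listed.

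On matching and timing, the section says "They will be age-matched to the study participants" and, for that reason, "they will be recruited by the end of recruitment for the main study, so that the age distribution of the participants is known". It mentions no matching on calendar time, site or sex.

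The trial's own definition of MAM (Summary, Participants; section 3.1.2) is a weight-for-height z-score from -3 to below -2, or a MUAC from 115 to below 125 mm. Section 3.1.3 has a separate rule for children admitted on MUAC, so this is a working route of entry.

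On dates, section 5 says "Recruitment of the children is expected to begin in August 2013 and last for 6 months", and Table 3 shows inclusion from August 2013 to January 2014. Section 3.1.13 lists "age, sex, MUAC, WHZ, season" as covariates for the lean body mass model. It describes no analysis for the thymus reference comparison.

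**The concern.** The reference group exists to show what the thymus looks like without moderate malnutrition. Two features of its design work against that.

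First, cases and comparators are defined on different scales. The trial accepts either of two indicators as evidence of MAM, and the reference group rules out only one of them. A healthy-looking child with a z-score above -1 and a MUAC of 120 mm meets both lists. Each such child in a group of about 30 pulls the reference mean towards the MAM mean if low-MUAC children have smaller thymuses.

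Second, the two groups are spread differently over calendar time. If thymus size shifts with season, part of any difference from the reference children would reflect when they were scanned. Section 1.4 describes recurrent food insecurity linked to rains and harvest, and the sponsor adjusts the primary model for season, so the question is a fair one to raise.

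At stake is the interpretation of this one contrast. Section 1.3 treats thymus size as a marker of the immune deficit of malnutrition, so a misread difference would matter for that argument.

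**Working it through.** The documents give no effect size, SD or sample-size basis for this comparison, so there is no stated figure to reproduce. The check has two parts.

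**Definitions side by side**

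| | Trial (MAM) | Reference group |
|---|---|---|
| Weight-for-height z-score | -3 to below -2, or the MUAC route | above -1 |
| MUAC | 115 to below 125 mm, or the z-score route | not listed |
| Age | 6 to 23 months | 6 to 23 months |
| Calendar time | August 2013 to January 2014 | tied to the end of recruitment |

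The overlap is any child with z-score above -1 and MUAC from 115 to below 125 mm.

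**What it could cost, on assumed inputs**

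Inputs: 30 reference children (section 3.1.11); two-sided 5% test and 80% power (assumed); m trial children scanned (not stated, so 100, 300 and 1608 are tried, the last being the whole trial). I take the comparison to be with baseline scans.

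1. Precision. In SD units, SE = √(1/30 + 1/m), and the difference detectable at 80% power is (1.960 + 0.842) × SE.
   - m = 100: SE 0.208, detectable 0.58 SD
   - m = 300: SE 0.191, detectable 0.54 SD
   - m = 1608: SE 0.184, detectable 0.52 SD

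2. Dilution. Suppose a share f of the reference children are MAM by MUAC and have the same mean thymus size as the trial's MAM children. The contrast shrinks to (1 - f) of its true value. Where power would be 80%, it becomes Φ(2.802 × (1 - f) - 1.960):
   - f = 0: 80%
   - f = 5%: 76%
   - f = 10% (3 of 30): 71%
   - f = 20% (6 of 30): 61%

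3. Season. Suppose enrolment is even, all reference scans fall at the end of the window, and thymus size drifts linearly by D SD across it. Trial children average D/2 of the drift and reference children carry all of it, so the bias is D - D/2 = D/2.
   - D = 0: no bias
   - D = 0.2: bias 0.1 SD, type I error about 8%
   - D = 0.4: bias 0.2 SD, type I error 16% (m = 100) to 19% (m = 1608)

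The documents supply neither f nor D.

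**The case against.** There is a good case that the plan already contains most of what is needed.

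- The group is described as well-nourished, and section 3.1.2 has every child brought to the centres screened for trial eligibility, MUAC included. While recruitment is open, a child with MUAC 120 mm should be noticed. This reduces the risk but does not remove it. The operative list is still weight-for-height only. A low-MUAC child who stays outside the trial, because the caretaker declines, the household plans to move, or a sibling is already enrolled (section 3.1.8), still meets that list.
- Reference children have anthropometry taken, and in the trial that includes MUAC, so any overlap should be visible and reversible. This stands, but no such exclusion is planned.
- Late recruitment is deliberate, because it allows matching to the participants' final age distribution. That is a legitimate trade-off. The phrase used is by the end, so recruitment only at the end is an inference, though the stated reason supports it.
- No passage says that thymus size varies with season, and season is named only in the lean body mass model. This stands.

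A reader might infer that season and group cannot be separated by any adjustment. That is not so. Trial enrolment runs through January 2014, so late-enrolled MAM children overlap the reference scans in calendar time, and adjustment or restriction is possible. The valid criticism is that neither is planned.

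A reader might also compute 1608/6 = 268 and take that as the number of MAM children scanned in the same month. The documents do not support this: only a subgroup is scanned, its size and accrual are not given, and nothing says that all reference scans fall in one month.

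**Conclusion.** The point holds in a limited form. The missing MUAC criterion is a plain gap, because the written rules allow a child who is MAM by the trial's own definition to be counted as well-nourished. The timing leaves the contrast open to seasonal confounding, with no analysis specified to deal with it.

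It would go too far to conclude that the contrast is in fact diluted or confounded. That would need a low-MUAC share and a seasonal drift that the documents do not report, and both could be zero. The power and bias figures above show only how the result would respond to assumed values. The dilution figures further assume that low-MUAC reference children have the same thymus size as trial children.

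Severity is minor. This is a non-randomised side comparison with about 30 children. In section 2.2 thymic size appears as an outcome of supplementation, and the contrast with well-nourished children is not a listed objective. The randomised comparisons and the primary outcome are untouched.

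**What to change.** 1. Add MUAC of at least 125 mm to the reference-group inclusion criteria. If those children have already been recruited, exclude any with MUAC below 125 mm, using the anthropometry collected. The first option costs one measurement that trial anthropometry already includes. The second loses a few children from a small group.

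2. Deal with calendar time in one of two ways.
   - Spread reference recruitment over the enrolment window, about 30/6 = 5 children a month, matched in running age bands to the children enrolled so far. The numbers of children and scans do not change; the cost is slightly looser age matching.
   - Keep the present timing and pre-specify adjustment of the MAM-versus-reference comparison for calendar month, with restriction to MAM children scanned in the same period as a sensitivity analysis. Adjustment assumes an additive month effect. Restriction loses precision: with an assumed 300 children scanned and one sixth (50) retained, the detectable difference rises from 0.54 SD to 2.802 × √(1/30 + 1/50) = 0.65 SD. If all reference scans fall in one month and month is fitted as a category, the adjusted contrast rests largely on that same month.

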#### *3.1.12. Data management*

Data will be kept confidential and in a locked facility to which only the investigating study team will have access. All study forms and questionnaires will only be accessible to the study staff during the trial. After the trial completion, these documents will be transferred to University of Copenhagen and kept in a locked area for at least 5 years from the last patient. A copy of the data set will be kept at the study site, and will be managed by ALIMA.

Data will be anonymous. Individuals will receive a unique identification number and no names will be entered into a computer.

Data will be double entered into Epidata software by a locally recruited data management team supervised by the Study team. A data management plan will be ensured by the University of Copenhagen. Data will be entered on computers specifically dedicated to this task. Daily back-ups will be made on an external device (USB key or hard drive) dedicated to this task. Data will be sent by email regularly to the principal investigator and co-principal investigators in Europe. Data sent by email will not allow identification of involved subjects.

### 3.1.13. *Data analysis*

The main effectiveness criterion will be the mean change in lean body mass after 3 months of supplementation (absolute increase expressed in kg). The primary analysis will be conducted in the intention to treat (ITT) population and will therefore include all randomized subjects having at least one exploitable baseline and 3 months LBM measures,. The primary analysis will be conducted by means of a single statistical analysis including both main arms, ie LNS and iCSB:

- A three-way analysis of variance (ANOVA) will be used to evaluate if the two interventions modify the effect of dehulled soy and soy isolate at different levels of milk content.
- The ANOVA will also include LBM at baseline as well as a number of additional explanatory (age, sex, MUAC, WHZ, season) that adjust for potential differences present in the study population. To adjust for variation between centers random effects for each centre are also included in the model. Thus, the statistical model will be based on a linear mixed model.
- Pairwise comparisons of means within and across the two arms will be done using the linear mixed model. Multiplicity will be taken into account by adjusting all pairwise comparisons.
- The effect of supplementation, ie. the difference in mean changes in LBM at 3 months of each group will be presented in terms of estimated means with 95% confidence intervals.

All other statistical analyses of the primary endpoint, ie other study populations, sub-group analysis, and inside-the-table comparisons, and all statistical analyses of secondary endpoints, will be considered secondary analyses. These include:

- Evaluation of the effect of the type of soy by comparing, in the LNS and the iCSBs groups separately, the mean increase in LBM at 3 months over the two groups of soy quality (dehulled soy i.e. 3 groups merged, soy isolate i.e. 3 groups merged).
- Evaluation of the effect of the milk protein content by comparing, in the LNS and the iCSBs groups separately, the mean increase in LBM at 3 months over the three groups of milk protein content (i.e. 2 groups merged for each level of milk).
- Analysis might also be conducted among the subgroup of participants presenting these 2 LBM measurements and the per-protocol population (i.e. excluding participants with violation of protocol).

For all secondary analyses, no adjustment for multiplicity is planned.

### **Interim analysis**

Due to the relatively short recruitment period (approximately 6 months), no interim analysis will be conducted.

### **Safety analysis**

Safety analyses will be performed among participants having been randomized. The number of adverse events and serious adverse events will be presented for each group. Proportion of participants presenting with AE or serious AE will be compared between groups. Description of adverse events will be given.

Statistical analysis will be performed using Stata software.

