### *3.1.3. Interventions: food products and quantities, medical treatment and incentives*

#### **Food products and quantities**

Children will receive 500 kcal/day. Food will be distributed fortnightly during a 3 month period. At each visit, a ration will be given on the spot. Mothers will be asked to bring back the empty LNS packs at the next visit to give to the personnel charge of the supplement (not to staff involved in measurements, to ensure blinding).

CSB will be provided in bi-weekly rations, to be prepared at home.

During the entire follow-up, any child developing severe acute malnutrition (WHZ less than – 3 z-scores, MUAC <115 mm or edema) would be referred for treatment of SAM. The following children will be referred to Yako pediatric unit, which is supported by ALIMA, for medical evaluation;

- Children admitted based on WHZ  $\geq$  -3 - and < -2 z-scores who have not reached a WHZ  $\geq$  -2 z-scores at the end of the 3 months intervention
- Children admitted on MUAC  $\geq$  115mm and < 125 mm who have not reached 15% weight gain,
- Children presenting a weight loss  $\geq$  5% from his/her weight at baseline for two consecutive visits.

Should these children receive other nutritional intervention during their hospitalization, they will be withdrawn from the study as failures to respond to treatment. Data obtained after receiving other nutritional intervention than previewed will not be included for data analysis.

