| Serious Adverse Events                                                                                  | Local Foods                                          | Until the end of treatment                                                                        | - Outcome of the treatment
- Anthropometric measurements and clinical assessment until end of treatment                                   |
| Other                                                                                     |                                                      |                                                                                                   |                                                                                                                                              |
| Transfer to the ATFC or ITFC,                                                                           | RUTF or food as provided at the ITFC or the hospital | Until the end of treatment                                                                        | - Outcome of the treatment
- Anthropometric measurements and clinical assessment until end of treatment                                   |
| Hospitalization                                                                                         | Continue intervention                                | Until the end of treatment                                                                        | - Medical follow-up
Outcome of the treatment
- Anthropometric measurements and clinical assessment until end of treatment  |

 Participants who withdraw informed consent or were lost to follow-up will not receive further incentives. Other participants will receive the incentives according to the planned timing at the start of the study.

 Children receiving other nutritional intervention (which is not part of Study) after being referred, they will be considered as failure to respond to treatment, and data obtained after receiving other nutritional intervention than previewed will not be included for data analysis

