#### *3.1.10. Participants follow-up chart*

Active screening will be done within the community and children 6-23 months presenting at the CSPA will be assessed for eligibility. The caretakers of those eligible will receive detailed information by the study staff about the trial (see information notice in annex7) and will be invited to freely consent to participate. They will be asked to sign (or thumb-print if illiterate) the informed consent form (see in annex 8). An independent literate witness (from the community) will be required to be present during the reading of the consent form and sign in addition to the fingerprint requested from a non-literate study participant. After written informed consent has been obtained, children will be assigned a sequential study number.

This number will be reported on all the participant documents as well as on an identification bracelet and an identification card (that will include a picture of the child and his/her caretaker). Furthermore participation will be registered in the patient health card, to avoid that the patient seeks nutritional supplementation or treatment from other CSPS.

The participants will be assessed as described in the following Table 2. A participant will be considered as having missed the fortnightly or monthly visit if they present with a delay of more than one week. If the patient does not show up at the centre, after more than one week he/she will be visited at home to evaluate reasons for defaulting. Defaulting due to death will be reported with morbidity data

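### The rule that drops data after other feeding has no safety exemption, so serious adverse events and deaths after a child leaves the study food may go uncounted

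*Combined protocol and SAP*

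**What the plan says.** The safety analysis is a subsection of 3.1.13 (Data analysis). It defines who is analysed: "Safety analyses will be performed among participants having been randomized". It then says "Proportion of participants presenting with AE or serious AE will be compared between groups". It gives no period over which events count and says nothing about events after a change of food.

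The exclusion rule appears twice. In 3.1.3, under food products and quantities, it reads "Data obtained after receiving other nutritional intervention than previewed will not be included for data analysis". Footnote 2 of Table 1 (3.1.6) repeats it: "data obtained after receiving other nutritional intervention than previewed will not be included for data analysis". Neither place limits it to lean mass or growth, and neither exempts safety.

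Table 1 also sets what happens after referral. A child transferred to a therapeutic feeding centre receives "RUTF or food as provided at the ITFC or the hospital". A hospitalised child is to "Continue intervention". After a serious adverse event, a transfer or a hospitalisation, follow-up runs "Until the end of treatment", whereas section 5 promises three further months of follow-up for every participating child.

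Hospitalisation and death are also secondary outcomes under morbidity (3.1.5). Section 3.1.10 adds: "Defaulting due to death will be reported with morbidity data".

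**The concern.** The population and the period of a safety analysis are separate choices. The plan makes the first and leaves the second to a general exclusion rule. An analyst who follows that rule to the letter keeps every randomised child in the denominator but removes events that follow RUTF or hospital feeding.

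Children reach other feeding because they became severely malnourished, failed to recover or lost weight. The exclusion therefore depends on the outcome of the allocated food. A product with more failures loses more of its later events, so its excess of serious events and deaths is understated. A larger sample would not correct this. The morbidity tables offer no protection, because the same rule, read the same way, covers them.

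There is a related gap in collection. If follow-up of a referred child stops when treatment ends, deaths between then and month 6 may not be recorded at all, and no analysis choice can recover them.

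**Working it through.** **Reading the text.** Four questions decide which events a literal analysis would lose.

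1. Does the rule mention safety? No. It is neither applied to safety nor lifted for it.
2. When does it start? Once other feeding is received. Events before that count, including the admission during which other feeding begins.
3. Does admission alone trigger it? No. Table 1 keeps hospitalised children on study food unless they are given something else.
4. Are later events collected? Yes, until the end of treatment: Table 1 records the treatment outcome, and 3.1.5 requires all serious adverse events to be reported. After that, Table 1 and section 5 disagree.

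**Group sizes.** The plan's own figures reproduce: 16/0.4² = 100 per group; 100/0.75 = 133.3, rounded up to 134; 12 × 134 = 1608. Each food type (LNS or iCSB) therefore has 6 × 134 = 804 children.

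**Events dropped.** The documents give no rates, so every rate below is an assumption. If a share f of children receives other feeding and a share r of those later has a serious event, the number dropped is N × f × r.

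| f | r | per 134 | per 1608 |
|---|---|---|---|
| 5% | 5% | 0.3 | 4.0 |
| 10% | 15% | 2.0 | 24.1 |
| 20% | 30% | 8.0 | 96.5 |

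**Effect on a comparison.** Let b be the six-month background risk, t the month of the move, and a the share of moves that begin with an inpatient admission. The footnote in 3.1.5 makes such an admission a serious adverse event, and it precedes the other feeding, so it is counted.

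- Occurring = (1 − f)b + f[1 − (1 − bt/6)(1 − a)(1 − r)]
- Counted = (1 − f)b + f[1 − (1 − bt/6)(1 − a)]

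Assume b = 3%, r = 10%, t = 1.5, and f = 10% in one food type against 20% in the other:

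| a | Occurring | Difference (points) | Counted | Difference (points) | Share lost |
|---|---|---|---|---|---|
| 0 | 3.77% v 4.54% | +0.77 | 2.78% v 2.55% | −0.23 | 26%, 44% |
| 2.3% | 3.97% v 4.94% | +0.97 | 3.00% v 3.00% | 0 | 24%, 39% |
| 10% | 4.66% v 6.32% | +1.66 | 3.77% v 4.54% | +0.77 | 19%, 28% |
| 25% | 6.00% v 9.00% | +3.00 | 5.26% v 7.51% | +2.26 | 12%, 17% |
| 100% | 12.70% v 22.40% | +9.70 | 12.70% v 22.40% | +9.70 | 0, 0 |

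The counted difference is zero when a = 1 − (1 − b)/(1 − bt/6) = 1 − 0.97/0.9925 = 2.3%. With b from 1% to 6% and t from month 1 to month 3, this point lies between about 0.5% and 5%. Above it, the difference keeps its direction but is too small.

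**Deaths.** An earlier admission does not restore a later death to the death count. With b = 0.5%, r = 5% and the same f and t, the formulas with a = 0 give 7.7 v 11.4 deaths occurring per 804 and 3.7 v 3.4 counted. An excess of 3.7 deaths disappears from the table. The small counted gap the other way arises because the model gives children about to be moved no more than background risk; it should not be read as a reversal.

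**The case against.** The strongest reply is that no sentence applies the exclusion rule to safety. The safety section names its own population, wider than the primary analysis set, which needs lean mass at both times. Section 3.1.5 has all serious adverse events reported. Counting every reported event in every randomised child is a natural reading.

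The rule's placement also leaves its scope open. In 3.1.3 it follows the list of children referred to Yako for evaluation, after the separate sentence on children who develop severe malnutrition. In Table 1 the footnote is marked on the hospitalisation row, not the transfer row, and RUTF after transfer is itself foreseen in the table. Table 1 lists transfer and hospitalisation apart from withdrawals, so follow-up to month 6 may be intended.

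All of this stands as far as it goes. It shows that the exclusion comes from a literal reading and is not an expressed safety rule. It does not settle the matter: the rule's wording is general, no passage lifts it for safety, and two careful analysts could report different numbers of deaths per product.

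A reader might infer that the rule would make the worse food look safer. The documents do not support that. The negative difference in the first row of the second table needs almost no move to begin with an admission. Section 1.4 describes outpatient as well as inpatient treatment of severe malnutrition, so that share is not 100%, but zero is not credible either. Nor may a reader infer that children's care is at risk, since individual events still go to the trial manager and the ethics board.

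**Conclusion.** The point holds as a gap in a stated rule. Read literally, the plan omits serious adverse events and deaths that occur after other feeding begins while keeping the child in the denominator. The consequence is attenuation of product differences in serious events, and later deaths missing from the count.

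The size rests wholly on assumed rates. It runs from about 0.3 to 8 events per group of 134 over the range shown, and it is nil for the proportion with a serious event if every move starts with an admission. If both groups have the same rate of moves and the same risk afterwards, the comparison is not tilted towards either food, but events are still missed (26% of affected children at f = 10% and a = 0).

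Full counting removes the bias without giving much power: about 12% for 804 v 804 in the case with a = 0. The primary outcome is outside this point. The change should be made, because the correction is cheap and deaths by product ought to be countable in this population.

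**What to change.** - In 3.1.3 and in footnote 2 of Table 1, add that the exclusion does not apply to adverse events, serious adverse events, hospitalisation or death.
- In the safety analysis, state that for every randomised child these events are counted under the allocated product from randomisation to month 6, whatever food the child later received. Add a second table limited to events before any other feeding.
- In Table 1, bring follow-up after a serious adverse event, transfer or hospitalisation into line with section 5: continue to the end of treatment as now, then record vital status and admissions at months 3 and 6.

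The cost is a few sentences and some extra contacts; home visits are already planned for children who miss visits. Events after a move also reflect the other treatment, which is why the second table is kept.
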